## Abstract

**Introduction:**

The primary health care system provides an ideal setting for the integration of oral health into general health care as well as equitable access to oral health care. However, the limited oral health knowledge of primary health care workers necessitates appropriate training before they can participate in health promotion efforts. This pilot training was designed to examine the impact of the Oral Health Education module for Nurses and Community Health Care Workers on their oral health awareness and referral practices.

**Methods:**

This study will utilize a quasi-experimental design (pre-and post with a non-equivalent control group) to assess the impact of a five-day pilot oral health education program on the knowledge and referral practices of Nurses and Community Health Workers in primary health care centers in three states in Nigeria-(Lagos, Oyo, and Kano). The training modules were developed based on the six iterative steps described in the intervention mapping framework – needs assessment, highlighting program objectives and outcomes, selection of theory and mode of intervention, designing program based on theory, designing implementation plans, and developing an evaluation plan. Only the intervention group will participate in the full educational training sessions but both groups will complete the pre-and post-intervention questionnaires.

**Discussion:**

This pilot training combined the standardized training modules from the recently launched “*Oral Health Training Course for Community Health Workers in Africa”* and a newly developed maternal and child oral health module by our group using an evidence-based approach. To the best of our knowledge, this is the first program to examine the impact of the standardized OpenWHO modules. The success of this training will lay the foundation for developing a sustained channel for providing oral health education at the primary health care level in Nigeria, West Africa, and Africa.

## Introduction

Oral diseases and conditions are the most common non-communicable diseases (NCDs) and are increasingly becoming a global public health concern. Despite being largely preventable, about 50% of the global population (~3.5 billion) have some form of oral disease condition (1, 2). In 2019, about 44% of the population in the World Health Organization (WHO) African Region was affected by oral diseases. This data reflects the highest increase in the prevalence of oral conditions across the world over the past three decades (2). Regarding the burden of oral diseases in Nigeria, the 2019 estimates provided by the WHO reported a prevalence of 35.5% for deciduous caries (aged 1–9 years), 23.9% for decay on permanent teeth (aged ≥5 years), 25.1% for severe periodontal disease (aged ≥15 years); 7.9% for edentulism (aged ≥60 years) and a 1.2% age-standardized incidence rate of lip and oral cancer (2).

Adopting a preventive approach to oral health and integrating oral health into general health care is now a global health priority and is essential to achieving a broader impact on the community and population level and cost-effectiveness, especially in settings with limited healthcare resources (2–5). Access to preventive interventions, early disease detection and management, and more equitable access to comprehensive, high-quality care are just a few possible benefits of oral health-primary care integration (6, 7). However, many Nigerians do not have access to preventive dental care; as such, it remains an unmet health need (3).

In Nigeria, there is persistent difficulty in accessing oral care and inequalities in oral health outcomes as the oral health care system is characterized by limited resources, an overstretched workforce, high out-of-pocket expenses, the predominance of a private dental service model and little or no access for rural communities (8–14). Despite the appearance of progress in oral health-related matters, as evidenced by the introduction of the 2012 National Oral Health Policy (NOHP), which highlighted the role of PHC workers in integrating oral health with general health, efforts made to implement this comprehensively have failed due to limited resources (15). Furthermore, the persistent shortage and current decline in the Nigerian oral health workforce (1 dentist to 40,000 people) highlight the ongoing challenge of inadequate personnel in this country (9) and further bolsters the need to utilize and train midlevel and allied health workers to share and shift the current task burden (2, 8, 16).

In the present day, Nigerian PHCs rarely or sparingly provide oral health care (15). The direct connection of the PHCs to communities and individuals makes it the ideal platform for reaching the “*last mile*” population, primarily found in rural and underserved areas (7, 15, 17). PHC staff, including community health workers and nurses, are trusted members of the community. Exposing them to oral health education would provide them with a channel to amplify accurate health information within their communities while improving awareness about the burden of oral diseases. This could help promote health and oral health-seeking behaviors as well as prioritization of interventions for prevention and management. It is thus essential to adequately educate PHC workers before enrolling them on oral health promotion efforts, since research has revealed a lack of exposure to oral health education via their traditional training (18). Furthermore, successes from community-driven oral health promotion practices in Africa have been reported in countries such as Burkina Faso, Kenya, Cameroun, and Gambia (7). However, the absence of a model upon which oral health promotion can be built is a significant barrier to program implementation (18). This is because the application of sound and evidence-based models and theories provide a foundation for program planners to design, implement and evaluate effective health promotion programs (19). One such approach is Intervention Mapping (IM). IM is a planning framework useful for interventions targeted at behavioral change (20). It provides a template for the systematic planning, development, and evaluation of health promotion interventions (21, 22). IM has been characterized by three perspectives; the use of empirical evidence and theories, an ecological approach and stakeholder participation (20, 21), the outcome of which is more effective interventions (22). Despite its use in developing and implementing health interventions across the globe, there is a paucity of information on its use in health promotion planning in Nigeria, particularly in relation to oral health promotion.

The recently launched OpenWHO oral health promotion course for community health workers in Africa provides an opportunity to train PHC workers with standardized training modules, promoting consistency among trainees while serving as a foundation for improvement in the future (23). Moreover, a focus on vulnerable population groups such as infants, young children and pregnant women, who are usually disproportionately affected by gaps in oral health care (24, 25) via increased awareness and training on maternal and child oral health (MCOH) will allow for the provision of culturally appropriate health information for common oral diseases. These oral diseases include debilitating conditions such as orofacial cleft and Noma and training PHC workers will help foster community support and end the stigmatization associated with these conditions. Based on the six iterative steps described in the IM framework, this paper presents the protocol for Project OHE-NCHeW (oral health education module for Nurses and Community Health Care Workers).

## Methods

### Program development using the IM framework

The week-long educational intervention was designed using the iterative steps of the IM framework (Figure 1). Step 1 involved conducting a literature review by searching public databases for existing peer-reviewed literature, policy documents and organizational reports to explore the barriers and inequities in accessing quality and comprehensive oral care in developing countries such as Nigeria. Specific focus was placed on the integration of oral health into general health care services. The opinions of key stakeholders consisting of a multidisciplinary team of experts at different levels of the health care system, including dentists and dental public health practitioners, public health practitioners (with vast experience in oral health education, promotion and programming) (26–30), nursing educators, community health educators, industry partners, policymakers, nurses, and community health workers were also sought to answer these questions. Oral health integration, specifically in the PHC system, has been described as an efficient and cost-effective way of promoting population oral health in developing countries (2, 3, 8, 30, 31). The information obtained from the knowledge gaps identified in the literature and stakeholder engagement guided the development of program objectives and outcomes using a logic model in step 2 (Table 1).

**Figure 1 fig1:**
[figure not shown]
Intervention mapping steps adapted from planning health promotion programs (21).

**Table 1 tab1:** Logic Model.

Resources	Activities	Outputs	Short & Long Term Outcomes
Project Working Group. Time for planning and implementation. Project Funding from Industry Partners (Colgate-Palmolive and National Dental Association Foundation). Training Materials. Partners at Dental Colleges and State Department of Health.	Mobile *PHC workers and community support. Design training and workshop materials. Implement training strategy. Promote community oral health education. Create an evaluation plan.	# of *CHWs & Nurses trained. # of *OHE sessions completed/3months. # of PHC patients who have received OHE/3 months. # of patients referred to dental centers for oral conditions/three months.	**Short term** Increased *OH knowledge and awareness among participants. Change in patient attitude about the need for oral health care. Increased # of referrals to dental centres. **Long term** Increased competency among PHC workers in providing OHE. Incorporation of OHE into the training curriculum of PHC workers. Increased use of preventive oral care services. Decreased prevalence of oral health disease conditions.
**Assumptions** Limited oral health training restricts the ability of PHC workers to provide adequate oral hygiene education. To start this process, those on ground would require some assistance to start. PHC workers and other stakeholders are interested in and fully supportive of the project.		**External Factors** Continuation of funding for training activities. Availability of time for PHC workers to incorporate OHE into health promotion activities.	

*PHC, Primary Health Care; OH, Oral Health; OHE, Oral Health Education; CHW, Community Health Worker.

In step 3, we identified an evidence-based approach most likely to influence change using the Lay Health Worker Model/Promotora de Salud (32), a public health model of workforce development targeted at health professionals such as community health workers, in this context, who lack formal oral health training but are members of the communities that they work in (33, 34). This model is often utilized to improve and support access to care in settings with workforce shortages (35). Although this is not commonly used in this population, the promising outcomes reported as it concerns oral health-related knowledge and behaviors in minority populations (36–39) and the need for a more competent allied health workforce capable of providing culturally appropriate oral health care in Nigeria makes it applicable to this study. By exploring parallel processes through collaborative partnerships and considering cultural nuances in the curation of training materials to maximize relevance and acceptability, we anticipate an impactful and lasting program outcome. This led to the fourth step, where program components, like training modules, assessment questions, activity sheet and the logbook for evaluation, were designed following extensive deliberation with all stakeholders. For the fifth and sixth steps, we established how, when, and where the training will be implemented and developed an evaluation plan to assess the effectiveness of the program. In this case, the impact of OHE-NCHeW will be immediately evaluated post-intervention and after 3 months in the training and intervention group.

### Study objective

This study aims to report the experience of adapting, developing, facilitating, and evaluating a five-day pilot of the modules for Project OHE-NCHeW in three states in Nigeria. This training seeks to examine the impact of the standardized OpenWHO oral health promotion modules and an additional Maternal and Child Oral Health (MCOH) module on participants’ oral health knowledge and referral practices as they relate to oral health. This pilot is intended to serve as a foundation for promoting oral health knowledge among primary care workers in the country. Our long-term objective with this systems-level intervention is to increase the capacity of PHC workers (Nurses and Community Health Workers) to provide oral health promotion via oral health education and engage patients attending PHCs to promote primary prevention methods for oral health in a bid to reduce risk for oral diseases.

### Research question

Does the introduction of oral health education modules by designated trainers improve the oral health knowledge, attitude, and referral practices regarding oral conditions in PHC Nurses and CHWs?

#### Null hypothesis

No measurable difference will be observed in the post-intervention knowledge scores and referral practices as it relates to oral health between participants with access to the 5-day training workshop vs. the control group.

#### Alternate hypothesis

An observable difference will be present in post-intervention knowledge scores and referral practices as it relates to oral health between participants with access to the training workshop vs. the control group.

### Study design

We will utilize a quasi-experimental design (QED) (pre-and post-with a nonequivalent control group) to assess the impact of a five-day pilot oral health education program on the knowledge level and referral practices of Nurses and Community Health Workers in PHCs in three States in Nigeria - (Lagos, Oyo and Kano). A three-month post-training evaluation will follow this. A pre-training evaluation will be conducted prior to the commencement of training, and a post-evaluation will be conducted immediately and 3 months after training. Furthermore, we have included a qualitative assessment via unstructured interviews with the program trainers to explore their experience delivering the training modules and interacting with participants. We will also conduct a focus group discussion (FGD) with the participants in the intervention group to have an in-depth understanding of their opinions, training impact and points of improvement at the 3-month post-training evaluation. Quasi-experiments are often conducted to assess the effectiveness of a treatment, such as educational intervention in field settings where random assignment is not feasible (40–42). This method remains a quick and convenient approach to evaluating a target group to which an intervention has been applied (43).

### Sample size estimation

For the feasibility of pilot studies, research has shown that a sample size consisting of 30 participants in a group is sufficient (44, 45). Based on this evidence, we plan to recruit a minimum of 10 and a maximum of 20 nurses and community health workers in each group per study site. Overall, the estimated sample size for the quantitative component of this pilot study across the three study sites is 120 (60 participants in the intervention group and 60 participants in the control group). The data obtained from this pilot program will be used to estimate a suitable sample size for our major study in the future (46). For the qualitative assessment, unstructured interviews will be conducted with the trainers. A full-group focus group discussion [>7 participants per group as defined by Cortini et al. (47)] will be conducted at each study site. For this study, we intend to engage 8–10 participants per site.

### Participants

For each study site, 40 participants (20 interventions and 20 controls) will be selected from a minimum of 4 PHCs. Participant selection will be by cluster sampling in each study site. In order to prevent cross-contamination among the participants, those in the intervention and control groups will be selected from different centers. Eligible participants will be 18 years and older, who speak and respond to questions in English, are employed full-time as a Nurse or CHW at the selected PHCs, have had no previous exposure to oral health training, and be willing to participate in the study. Participants with previous exposure to oral health training and those who cannot commit to the entire duration of the training will be excluded from the study.

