### Participant recruitment

The permission to conduct the study was sought, and relevant approvals were obtained from the Permanent Secretary (PS) of the State Primary Boards, Permanent Secretaries of State Health Districts, Director of Nursing Services and the Director of Community Services. Nurses who are in the dental and maxillofacial unit and/or nurses who have assisted with Smile Train education and surgeries were excluded. The nominal rolls of nurses and community health workers in the State Health Districts served as the sampling frame, and five nurses and five community health workers who met the selection criteria were selected from each district by simple random sampling (balloting). To avoid contamination, participants from Health districts who were from more distant locations were selected for the control group, while the participants from locations closer to the training center were selected for the intervention group. Following the IRB approval from the Ethics Committee of the participating centers, each recruited participant signed a written consent before active recruitment into the study.

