### Data analyses

Quantitative data analysis will be conducted using SPSS version 28. Univariate analysis presenting the frequencies and percentages for categorical variables and the means and standard deviation (SD) for the continuous variables will be performed. For the bivariate analysis, t-tests and ANOVA or their nonparametric analogs (based on normality) will be conducted for within and between group associations with a *p*-value set at <0.05. For the qualitative data analysis, audio recordings obtained during data collection will be transcribed verbatim by the research team and will be analyzed by content analysis. Data will be analyzed using Nvivo12. Responses will be coded into themes and sub-themes, ensuring data saturation when no new information is discovered in data analysis. Comparison, mapping, and verification of conclusions will be conducted and arranged according to the study objectives. Prominent quotes from the participants will be selected and cited within the report.

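### Whole centres or districts sit in one arm, but the named between-group tests treat participants as independent

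*Protocol article*

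**What the plan says.** The protocol article describes the sampling and assignment unit in two ways.

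- **Participants** specifies cluster sampling within each site, with "40 participants (20 interventions and 20 controls) will be selected from a minimum of 4 PHCs". The arms are separated by facility: "In order to prevent cross-contamination among the participants, those in the intervention and control groups will be selected from different centers".
- **Participant recruitment** draws instead on the staff rolls of the health districts: "five nurses and five community health workers who met the selection criteria were selected from each district by simple random sampling (balloting". More distant districts supply the controls and nearer ones the intervention group.

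Under **Sample size estimation**, "Overall, the estimated sample size for the quantitative component of this pilot study across the three study sites is 120", with 60 in each group. The range allowed is wider: "we plan to recruit a minimum of 10 and a maximum of 20 nurses and community health workers in each group per study site". The basis is a rule for pilot feasibility: "research has shown that a sample size consisting of 30 participants in a group is sufficient". The pilot data are also to be used to size a later major study.

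Under **Data analyses**, "t-tests and ANOVA or their nonparametric analogs (based on normality) will be conducted for within and between group associations", at a 0.05 threshold. **Intervention and control** adds that the groups are compared at each study site. No section mentions an ICC, a design effect, a cluster term or an adjustment for state.

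**The concern.** Workers in one facility or district share supervision, patients and access to dental referral. Their knowledge scores, and still more their referral counts, are likely to be correlated. Because no cluster contributes to both arms, that correlation does not cancel in the between-group comparison. The variation between clusters becomes part of the apparent training effect, while a participant-level test computes its standard error as if that variation were absent.

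Two things are at stake. A p-value below 0.05 could reflect differences among a handful of centres or districts rather than the training. The pilot is also meant to inform a larger study, which will need the ICC as well as the standard deviation if it recruits in the same way.

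**Working it through.** **The plan's own figure.** 3 sites × 2 groups × 20 = 120, or 60 per group. This reproduces. There is no power formula behind it to check.

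**Number and size of clusters.**

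- District description: 5 + 5 = 10 per district; 20 / 10 = 2 districts per arm per state; 2 × 3 = 6 per arm; 12 in all.
- Centre description: 40 / 4 = 10 per centre on average. Four centres is a minimum, so 10 is the largest possible average. With 8 centres per site the average is 40 / 8 = 5, which gives 4 centres per arm per state.

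The check therefore uses cluster sizes m = 10 and m = 5.

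**Assumptions not in the document.** ICC of 0.05, 0.10 and 0.20 (and 0.01 as a low case); equal cluster sizes; a two-sided test; a pooled comparison of 60 with 60.

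**Formulas.**

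- Design effect: DE = 1 + (m − 1) × ICC
- Effective number per arm: 60 / DE
- True standard error: √DE times the naive one
- Real error of a nominal 5% test: 2 × [1 − Φ(1.96 / √DE)]

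For example, with m = 10 and ICC = 0.10: DE = 1 + 9 × 0.10 = 1.90; 60 / 1.90 = 31.6; √1.90 = 1.38; error = 2 × [1 − Φ(1.96 / 1.38)] = 0.155.

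| m | ICC | DE | Effective n per arm | True / naive SE | Real error |
|---|---|---|---|---|---|
| 10 | 0.01 | 1.09 | 55.0 | 1.04 | 6.0% |
| 10 | 0.05 | 1.45 | 41.4 | 1.20 | 10.4% |
| 10 | 0.10 | 1.90 | 31.6 | 1.38 | 15.5% |
| 10 | 0.20 | 2.80 | 21.4 | 1.67 | 24.1% |
| 5 | 0.05 | 1.20 | 50.0 | 1.10 | 7.4% |
| 5 | 0.10 | 1.40 | 42.9 | 1.18 | 9.8% |
| 5 | 0.20 | 1.80 | 33.3 | 1.34 | 14.4% |

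**Simulation check.** In 20,000 runs with 6 clusters of 10 per arm, the ordinary t-test rejected a true null in 10.5, 15.3 and 24.8% of runs at ICC 0.05, 0.10 and 0.20. A t-test on the 12 cluster means (10 degrees of freedom) stayed at about 5%.

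**State differences.** The arms are balanced across states, so state variance left in the error term makes a pooled test more conservative. With a state variance of 0.3, against 1 for cluster and individual variance together, and clusters of 10, the simulated error is about 8, 12 and 21%. The offset is partial at these values and depends on how large the state differences happen to be.

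**Site-by-site comparison.** With 20 per arm per site in clusters of 10, each comparison sets 2 clusters against 2. A cluster-level test then has 2 + 2 − 2 = 2 degrees of freedom.

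**The case against.** The strongest objection is that this is a non-randomised pilot with no power claim. The Discussion already concedes selection bias, uncontrolled factors and no causal inference. Where the arm depends on distance from the training centre, the exact error rate is secondary to confounding. That stands as a reason to rate the point lower. It does not remove it: the article states hypotheses of a between-group difference, sets a significance threshold, and does not list clustering among its limitations.

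It could also be said that the detail belongs in an unseen analysis plan. That does not stand, because the article itself names the tests, and they do not fit the sampling it describes.

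Several stronger readings are tempting but not supported:

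- **Clusters of 10 throughout.** This is exact for districts only. For centres it is an upper limit on the average.
- **One pooled test of all 120.** The article does not state it and speaks of comparison at each site. The table is therefore an illustration. Testing by site does not escape the problem, since it leaves fewer clusters.
- **Effective numbers fall below the plan's own benchmark of 30.** That benchmark is offered for pilot feasibility, not precision, so it is not a yardstick for effective sample size.
- **The major study will be too small.** The article says only that pilot data will be used to size it. Nothing says that the ICC will be ignored.
- **Every named test is affected equally.** Stable differences between clusters cancel in paired changes within a group, so those tests suffer less.
- **One ICC range fits both units.** Workers drawn from a district roll need not share a facility, so the district ICC may differ from the centre ICC.

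The two sampling descriptions are partly compatible, since different districts necessarily contain different centres. They still define different clusters.

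**Conclusion.** The between-group analysis is wrong for the design as written. Under both descriptions of sampling, whole clusters belong to one arm, and the named tests ignore this. For any positive ICC within states the naive standard error omits between-cluster variance, and the false-positive rate exceeds 5% unless large state differences left in the error term happen to offset it.

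The direction follows from the documents; the size does not. It rests on the assumed ICC, the assumed cluster size and an assumed pooled comparison. Over ICC 0.05 to 0.20 the real error runs from about 7% (clusters of 5) to about 24% (clusters of 10). If the ICC is near 0.01 the matter is minor.

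This should be fixed before analysis. It is not a wrong power calculation, because none is claimed.

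**What to change.** 1. Reconcile Participants with Participant recruitment: name one sampling and assignment unit, and record its identifier for every participant. Without the identifier the analysis cannot be corrected later.
2. Replace the participant-level between-group tests with a mixed model: random intercept for that unit, state as a fixed effect, and small-sample degrees of freedom (about 12 − 1 − 2 − 1 = 8 if there are 12 clusters). An equivalent cluster-level analysis pooled across states would also serve. Treat site-specific comparisons as descriptive.
3. In Sample size estimation, state the number of clusters per arm and say that 60 per group is not 60 independent observations. Do not enter an effective sample size as if known, because it would rest on an assumed ICC.
4. Report the ICC and standard deviation with confidence limits as inputs for the major study.

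The cost is revised wording and one data field, with no extra participants. Confidence intervals will be wider, and an ICC from so few clusters will be imprecise. The change does not cure confounding by distance, which remains a limitation to report.
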